### Exposure

The exposure of interest is electronic cigarette use, referred to as ‘vapes’. Nicotine exposure is objectively determined by sampling urine cotinine in the third trimester. Urine cotinine is a metabolite of nicotine, and accepted, reliable reflection of recent nicotine use; it is the most widely used biomarker for the metabolism of nicotine in the human body with 70–80% of nicotine being converted to cotinine in the liver, of which 10–15% is excreted in the urine; it is a highly specific and sensitive marker for nicotine use in the short term [39]. Cotinine has a longer half-life in comparison to nicotine (19 versus 2 h), and therefore is helpful in determining nicotine use over the course of days rather than hours in the case of BCO [40].

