**Methods:**

Pregnant women attending three, large, standalone, urban, university, maternity units in Dublin, Ireland, will be invited to take part in this prospective, multicentre, observational cohort. Smoking and vaping patterns will be assessed using digital patient questionnaires. Objective assessment of breath carbon monoxide and urine cotinine levels will accurately determine exposure status at pre-specified timepoints. A third trimester ultrasound will assess growth and fetal dopplers across all groups. Postnatally, infants will undergo anthropometric measurements and developmental checks. A subgroup of 150 randomly selected infants will be assessed with the Bayley’s Scales of Infant and Toddler Development.

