### Electronic cigarettes/vapes

Electronic cigarettes, colloquially known as ‘vapes’, are battery powered devices that heat a solution (e-liquid) to create a nicotine-containing aerosol. In addition, the e-liquid often contains different flavourings, as well as the compounds propylene glycol and glycerine. The evaporation of the liquid at the heating element is followed by rapid cooling to form an aerosol which is directly inhaled (or “vaped”) by the user through a mouthpiece. Each device includes a battery, a reservoir that contains the liquid, and a vaporisation chamber with a heating element [28]. The newest generation E-cigarette devices facilitate blood serum nicotine concentrations that are equivalent to that of a traditional combustible cigarette [29]; the method of use is similar to conventional combustible cigarettes resulting in an experience for the user that is closer to cigarette smoking than any other forms of NRT, and likely explains the growing popularity of vapes as a smoking cessation tool [30]. Importantly, vaping does not generate carbon monoxide, the primary, deleterious by-product of combustible cigarette smoking.

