## Objectives

The ECHO study has four primary objectives described below:The primary obstetric objective is to establish whether infants born to women who vape are at a higher or lower risk of adverse outcomes in pregnancy compared to infants of combustible cigarette smokers and non-smokers.The primary neonatal objective is to assess anthropomorphic variation, if any, in newborn babies born to vapers in comparison to smokers and controls. The primary paediatric objective is to establish whether parent-reported and doctor-confirmed wheeze and/or asthma occurs more frequently in children exposed to vaping in utero compared with children of combustible cigarette smokers and non-smokers.The primary neurocognitive objective is to assess if there are significant differences in neurocognitive outcomes between the infants of a women who vape compared to infants of women who used combustible cigarette smokers and non-smokers.Globally, we aim to correlate, obstetric, neonatal, pulmonary, growth and neurocognitive differences, if any, to quantitative levels of cotinine excreted in maternal urine at in the third trimester.

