### Population

This prospective, multicentre, observational cohort will focus on women pregnant with a singleton fetus who self-report vaping, cigarette smoking, vaping and cigarettes smoking, or no exposure (controls). The obstetric portion of the study operates from three recruitment sites; The Coombe Hospital, The Rotunda Hospital, and the National Maternity Hospital—these standalone maternity units, based in Dublin, Ireland’s capital city, cumulatively deliver approximately 22,000 women annually [31–34].

Smoking and vaping patterns will be assessed using a combination of digital validated patient questionnaires administered at set timepoints throughout pregnancy, in addition to objective assessment of exhaled breath carbon monoxide (BCO) assessed by point of care exhaled carbon monoxide breathalysers (Bedfont’s ‘Smokerlyzer’® device) at each antenatal study visit. Nicotine levels will be assessed using quantitative urinary cotinine, analysed by Eurofins Biomnis enzyme immunoassay.

Women are recruited prior to 24-week gestation after being directly asked about smoking and vaping status in a structured fashion at their booking visit; if they fulfil the eligibility criteria, they are then invited to partake in the study as either a vaper, a smoker, a smoker/vaper or a control (Table 1.).

**Table 1 Tab1:** Exposure status

Vaper	Vaper/smoker	Smoker	Control
• Reports vape use • BCO ≤4 ppm	• Reports dual use • BCO ≥ 5 ppm	• Reports cigarette smoking • BCO ≥ 5 ppm	• Denies cigarette smoking or vaping • BCO ≤4 ppm

A BCO measurement of ≥ 5 parts per million (ppm) was selected to define active smoking, in keeping with Irish National Clinical Guidance. Selection of BCO ≥ 5 ppm as a cutoff confers a sensitivity of 0.9 and specificity of 0.92 [35]. This is an important consideration in accurately classifying both smokers and smoker/vapers in addition to self-reported exposure status.

After screening, demographic and biometric data points are gathered, and a series of questionnaires are administered digitally as per the schedule outlined below:

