### Obstetric secondary outcomes

Trends in smoking cessation and crossover from smoking to vaping and from vaping to non-smoking/non-vaping/smoking.BCO at screening, 20 weeks, third trimester, and postnatally.Quantitative urine cotinine assay in the third trimester.Estimated fetal weight (EFW)—using the Hadlock formula [41]—fetal and maternal dopplers at 20 weeks and 32–34+6 (maternal: uterine artery Doppler, fetal: umbilical artery, middle cerebral artery, cerebroplacental ratio).Incidence of small for gestational age (SGA) defined as EFW and/or AC less than the 10th centile for gestational age on ultrasound at any gestation after study entry.Diagnosis of congenital malformation.Birth centile [42].Blood pressure measurement at screening, 20 weeks and third trimester, and postnatally.Incidence of essential hypertension—high blood pressure at booking defined at a BP 140/90 mmHg.Incidence of diagnosis of pregnancy-induced hypertension and incidence pre-eclampsia [43].Incidence of pre-labour premature rupture of membranes (PPROM).Incidence of anaemia, defined as a haemoglobin level of less than 10g/dL at booking, 28 weeks or any other time point in the antenatal period.Maternal history of abnormal cervical screening cytology or cervical surgery.Indication for and incidence of induction of labour.Mode of delivery.Delivery complications.Incidence of postnatal caesarean, episiotomy or perineal wound infection requiring antibiotics.Edinburgh Postnatal Depression Scores prior to discharge.Incidence of venous thromboembolic (VTE) disease—new onset deep venous thrombosis or pulmonary embolus.Unscheduled admission to hospital.Admission to high dependency unit (HDU) or inter-hospital transfer to intensive care unit.

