## Discussion

Vaping is an exposure that is undeniably increasing. The approach currently adopted in some parts of the UK is endorsement of vaping as a method of harm reduction in pregnancy; this pragmatic approach is occurring in a vacuum of evidence around safety, and challenges the advice that the medical community have historically offered to pregnant people—which is to abstain from potentially harmful exposures during gestation. Nicotine-containing vapes are addictive and their long-term impact on pulmonary, cardiovascular and neurological function in both adult and developing humans is undetermined. This study is ambitious as it aims to longitudinally assess the outcomes of the mother and baby dyad, examining not only the impact of vaping on pregnancy, but also on neonatal and infant health outcomes. A major strength of this study is the sequential assessment of breath carbon monoxide and urine cotinine to provide objective clarification of outcomes in relation to each exposure—previous large registry studies [52] have demonstrated higher levels of SGA and LBW in vapers; however, these data are drawn from post hoc questionnaires, and are subject to recall and selection bias. A prospective, observational cohort from The Coombe Hospital in Dublin found no difference in the incidence of SGA and LBW in vapers versus controls [46]. In addition, the robustly planned paediatric and neurocognitive assessment of exposed versus non-exposed infant will assist women, their midwives and doctors, to make informed health choices during pregnancy in the future.

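### A single third-trimester cotinine value cannot cover women who deliver before it is taken, and the vaper/control split rests on self-report that breath CO cannot check

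*Protocol article*

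**What the plan says.** **Timing of cotinine.** The Exposure section states: "Nicotine exposure is objectively determined by sampling urine cotinine in the third trimester". The Obstetric secondary outcomes list has the same single time, "Quantitative urine cotinine assay in the third trimester", and gives no gestational week. Breath carbon monoxide (BCO), in contrast, is listed at four times: "BCO at screening, 20 weeks, third trimester, and postnatally".

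**Use of cotinine.** After the four primary objectives, the Objectives section adds a global aim: to correlate obstetric, neonatal, pulmonary, growth and neurocognitive differences with "quantitative levels of cotinine excreted in maternal urine at in the third trimester". Table 2 makes preterm birth and low birth weight primary outcomes. The Population section places recruitment before 24 weeks.

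**Exposure groups.** Table 1 defines a vaper as a woman who reports vape use and has BCO of at most 4 ppm. A control "Denies cigarette smoking or vaping" and has the same BCO limit. Cotinine is not part of any Table 1 definition. The background section on vapes says: "Importantly, vaping does not generate carbon monoxide".

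**Claims made for the measurements.** The Abstract says that breath carbon monoxide and "urine cotinine levels will accurately determine exposure status at pre-specified timepoints". The Discussion says: "A major strength of this study is the sequential assessment of breath carbon monoxide and urine cotinine".

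**Missing data.** Multiple imputation will be considered if key measurements are missing at rates above 5%.

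**The concern.** There are two linked weaknesses in how exposure is measured, and in two places the article's wording hides them.

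First, a woman who delivers before the third-trimester sample has no cotinine value. In an analysis of cotinine against preterm birth, whether a value exists therefore depends on the outcome, and the earliest births are the ones missing. The result describes only women still pregnant at sampling, and nothing in the article says so.

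Second, the contrast in the study's first hypothesis is vapers against women who neither smoke nor vape. BCO removes active smokers from both groups but gives no information on vaping. A vaper who denies use and has a normal BCO is classed as a control. Such controls pull the vaper-versus-control difference towards the null, and a null finding could be read as reassurance in guidelines that the article expects to inform.

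The Abstract and Discussion present cotinine as a repeated, objective determinant of exposure status. The design sections give one late measurement that plays no part in forming the groups.

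**Working it through.** **Inputs from the article:** 3 × 400 = 1,200 women; preterm birth 6.2%; low birth weight 5%; smoking odds ratio (OR) for low birth weight 1.75; imputation considered above 5% missing; Table 3 detectable OR for preterm birth 2.04 at 400 per group. **Assumed, because the article gives no figure:** the share of preterm births before sampling (5% to 40%) and the share of controls who vape undeclared (2% to 10%).

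**1. The plan's own figure.** Two-sided 0.05, 80% power, pooled-variance two-proportion test without continuity correction, 6.2% baseline, 400 per group: the detectable OR is 2.04, as Table 3 states. Table 3 has no entry for the cotinine analysis.

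**2. Preterm births without cotinine.**
- Expected preterm births: 1,200 × 0.062 = 74.4.
- At 5%: 74.4 × 0.05 = 3.7, or 0.3% of 1,200.
- At 40%: 74.4 × 0.40 = 29.8, or 2.5% of 1,200.
- The 5% level corresponds to 1,200 × 0.05 = 60 women. Early births alone would reach it only if 60 / 74.4 = 81% of preterm births preceded sampling.

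**3. Effect on an odds ratio.** As an illustration, take 400 high-nicotine against 400 low-nicotine women with a true OR of 2.04. If shares s₁ and s₀ of the preterm cases are unsampled in the two groups, the odds among sampled women are multiplied by (1 − s₁) and (1 − s₀), so

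OR seen = 2.04 × (1 − s₁) / (1 − s₀).

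| s₀ | s₁ | OR seen | Power |
|---|---|---|---|
| 0 | 0 | 2.04 | 80% |
| 10% | 10% | 2.04 | 76% |
| 20% | 20% | 2.04 | 72% |
| 40% | 40% | 2.04 | 60% |
| 10% | 15% | 1.93 | 68% |
| 20% | 30% | 1.79 | 52% |
| 40% | 60% | 1.36 | 14% |

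Equal loss costs power only. Unequal loss also biases the OR. For birth weight as a continuous outcome this protection does not apply: the earliest and typically smallest babies are removed, which truncates the outcome.

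**4. Undeclared vaping among controls.** Let f be the share of labelled controls who vape and carry vaper-level risk: p_c′ = (1 − f)·p_c + f·p_v. With p_c = 0.05 and OR 1.75, the odds among vapers are 1.75 × 0.05/0.95 = 0.0921, so p_v = 0.0843.
- f = 2%: p_c′ = 0.0507, OR = 1.73.
- f = 5%: p_c′ = 0.0517, OR = 1.69.
- f = 10%: p_c′ = 0.0534, OR = 1.63.

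The 1.75 is the article's smoking effect, borrowed for scale. The article says that robust data on vaping are lacking.

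**The case against.** Much can be said for the plan, and several stronger readings fail.

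- **A reader might infer that the primary preterm comparison loses its early births.** It does not. Groups are set at recruitment before 24 weeks, and nothing says they are re-derived later. Only the cotinine correlation, which is not one of the four primary objectives, is affected.
- **A reader might place the urine sample at the 32 to 34+6 week scan.** That window belongs to the growth and Doppler item. No section ties the sample to it, and sampling early in the third trimester would lose few cases.
- **A reader might say that the loss violates missing-at-random.** Gestation at delivery is recorded, so missingness fixed by it depends on observed data. The difficulty is a different one: for a woman already delivered, third-trimester cotinine does not exist, and imputing it is extrapolation.
- **A reader might say that any nicotine effect on early delivery biases the result.** Step 3 shows that loss depending only on a binary outcome leaves the OR unchanged.
- **A reader might say that cases will be dropped.** No complete-case rule is stated, and handling such women is normally analysis-plan detail.
- **A reader might count users of nicotine replacement as misplaced controls.** The Note on nomenclature defines controls as women who use neither electronic nor combustible cigarettes, so such a woman fits the chosen definition. The background also reports no robust evidence of significant harm from nicotine replacement.

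It is also fair that self-administered questionnaires were chosen to improve reporting, that the BCO cutoff is offered for classifying smokers and dual users, and that 10% contamination is twice the roughly 5% vaping rate the article expects.

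What stands is that the cotinine value is certain to be absent after early delivery, the 5% rule would not be triggered by this loss alone, BCO cannot separate vapers from non-users, and the Abstract and Discussion claim a property that the design sections do not give.

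**Conclusion.** The point holds within limits. The global cotinine aim, applied to preterm birth, can only describe women undelivered at sampling. About 4 to 30 of some 74 expected preterm births would lack a value, if 5% to 40% precede sampling. The certain cost is power. Bias requires that the early share of preterm births differ by nicotine level, or that the outcome be continuous. The primary group comparisons keep all their births.

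The vaper/control split rests on self-report alone. Under the assumed 2% to 10% undeclared vaping with vaper-level risk, the attenuation is modest: an illustrative OR of 1.75 becomes 1.73 to 1.63. It works in the direction that makes vaping look safer relative to controls.

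The Abstract and Discussion wording is inconsistent with Table 1, the Exposure section and the secondary outcome list. None of this undermines the design. It is a cheap improvement worth making before analysis.

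**What to change.** 1. **Cotinine and preterm birth.** Analyse time to birth, with birth before 37 weeks as the event and delayed entry at the gestation of sampling. Do not impute cotinine for women already delivered. Report their number by exposure group, and label the result as conditional on being undelivered at sampling.
2. **Vapers versus controls.** Keep the Table 1 groups for the main analysis. Add a sensitivity analysis, for outcomes arising after sampling, that excludes controls whose third-trimester cotinine exceeds a pre-stated cutoff. Note reported use of nicotine replacement among those excluded, since it also raises cotinine. This check cannot verify status at entry or cover women who delivered before sampling.
3. **Wording.** Correct the Abstract and Discussion to say that exposure groups are set at recruitment by self-report plus BCO, and that cotinine is measured once, in the third trimester.

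The cost is one extra sensitivity analysis on data already planned, some analysis wording, and a more limited claim about cotinine and preterm birth. Eligibility, group definitions and sampling do not change.

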### Inclusion criteria

Women aged 18 or greater and less than 46 years of age at booking.Pregnant with a singleton fetus.Smoker or vaper or smoker/vaper or control.Able to understand and read English.Willing to agree to follow-up for the 2-year duration of the study in the postnatal period

### Exclusion criteria

Twins or higher order multiplesLate bookers—defined as booking after 24+0 weeks’ gestational ageFetus or infant diagnosed with a major congenital abnormality requiring immediate admission to NICU +/- outward transfer for surgery, chromosomal abnormalitiesAny inherited disorder of metabolism or cystic fibrosis on Guthrie cardHistory of significant maternal medical disorderHistory of significant maternal psychiatric disorder, e.g. delusional or psychotic disorders, use of >1 psychotropic drugs for treatmentSerious co-morbid addiction issues, e.g. opiate abuseSevere intellectual disability or lack of capacity

## Outcomes

### Primary outcomes

The primary outcomes outlined in Table 2 have informed the sample size calculation. As the outcomes for the postnatal psychological assessments are exploratory, we have used a pragmatic sample target of 150.

**Table 2. Tab2:** Primary outcomes

Primary outcomes		
Obstetrics/neonatal	Paediatrics	Psychology
• Preterm birth • Low birth weight	• Doctor-diagnosed wheeze	• Neonatal Behavioural Assessment Scale • Bayley’s Infant and Toddler Development (*n*=150)

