### Secondary neonatal outcomes

APGAR scores at 1 and 5 minutes.Brazelton’s Neonatal Behavioural Assessment Scale (NBAS).Umbilical artery blood gas (if available).Admission to neonatal intensive care (NICU) or special care baby unit (SCBU).Incidence of neonatal hypoglycaemia as per local guidelines.Incidence of neonatal jaundice requiring phototherapy.Mode and type of infant feeding.Neonatal anthropometric measurements (weight in grams, length, head, chest and waist circumference in centimetres).A subgroup of 150 infants will have PEAPOD assessment. The PEAPOD is a specialised scale that both weighs a baby and uses air displacement plethysmography to determine the baby’s body volume. These measurements allow us to calculate the baby’s density and estimate the baby’s body fat and lean body mass [41].

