**Table Taba:** 

Women who vape during pregnancy will be more likely have a preterm birth and that their infants will have a lower birth weight (LBW), lower neuro-behavioural scores and increased respiratory symptoms when compared with non-smokers.
Women who vape during pregnancy will be less likely to have a preterm birth and their infants will have a higher birth weight, higher neuro-behavioural scores, and fewer respiratory symptoms than when compared with tobacco smokers.

The best available data suggest a prevalence of smoking rate during pregnancy in Ireland is between 9 and 10% [44], whilst the current expected rate of vaping during pregnancy is approximately 5% [45]. The cumulative live birth rates in the three maternity hospitals in Dublin in 2023 were: The Coombe Hospital—6974, The Rotunda Hospital—8442, and the National Maternity Hospital—6880, which will give a projected denominator of approximately 22,000 total live births. The incidence of vaping during pregnancy in the Coombe is 5% [34, 46]; projected to the other three hospitals gives approximately 750–1250 vapers per annum. The calculations in Table 3 give the magnitude of a detectable association with (2-year) prevalence of each condition (odds ratios) or mean differences that are detectable at a power of 80%, with a type I error rate of 0.05. These assume use of simple uncorrected Chi-square test or *t* tests. Detectable effect sizes are presented assuming a range of sample sizes to illustrate how power is maintained under a range of recruitment scenarios. We plan to collect three equally sized groups—non-smokers, smokers, and vapers

**Table 3 Tab3:** Sample size calculation

Sample size (per group)	Baseline incidence		
	10% (wheeze)	6.2% (preterm birth)	5% (low birth weight)
	Detectable odds ratios:		
100	3.00	3.62	3.19
200	2.25	2.63	2.26
300	1.96	2.24	1.91
**400**	**1.80**	**2.04**	**1.74**

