Whilst robust data on the effect of vaping during pregnancy on women and infants are lacking, the effects of smoking are well characterised on neonatal anthropometric measurements. Asthma or wheeze has an incidence of approximately 10% within the first 3 years of life [47]. LBW occurs at a frequency of about 5% [48]. PTB occurs in approximately 6.2% of births in Ireland [49]. Maternal smoking has been shown to increase risk of asthma or wheeze in childhood with an odds ratio of 1.8 (95% CI 1.35–2.53). Smoking has also been shown to increase incidence of LBW with an odds ratio of 1.75 (95% CI 1.42–2.10). The odds ratio for PTB conferred by smoking is 1.27 (95% CI 1.20–1.33).

Data on neurocognitive outcomes is lacking; neurocognitive outcomes between groups can be expressed as standardised mean differences (SMD). Table 4 gives indicative detectable differences for each sample size. For reference, caregiver depression has been as a risk factor on the NBAS with a SMD of 0.28 [50] and smoking demonstrated an association of the order of SMD = 0.2–0.4 for executive function including inhibition and self-control [51].

**Table 4 Tab4:** Indicative detectable differences per sample size

Sample size (per group)	Standardised mean difference
100	0.40
200	0.28
300	0.23
**400**	**0.20**

Therefore, we propose to recruit 1200 participants (400 smokers, 400 vapers and 400 non-smoker, non-vaper controls) to generate adequate power and precision to answer our research questions.

In the case that key measurements are missing at rates in excess of 5%, multiple imputation procedures will be considered. We anticipate the likelihood of missing data is small given the standard procedures in place to manage the study centrally.

Case report form (CRF) data entry into REDCap will include extensive data validation checks. Missing data will be monitored, and strategies will be developed to minimise its occurrence. Central statistical data monitoring will summarise missing or inconsistent data periodically. The study workbook will be approved by the chief investigator and validations will also be made that will cross-check the study workbook with the ECHO study electronic CRF.

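### Birth weight is the stated neonatal question, but the primary outcome is the 5% low-birth-weight dichotomy, which has about 49% power at the cited odds ratio; mean weight would probably, though not certainly, be the stronger test

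*Protocol article*

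**What the plan says.** All of this is in the protocol article.

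- **Objectives:** "The primary neonatal objective is to assess anthropomorphic variation, if any, in newborn babies born to vapers in comparison to smokers and controls".
- **Power calculations and rationale, hypotheses:** compared with non-smokers, vapers are expected to differ in that "their infants will have a lower birth weight (LBW", with the abbreviation attached in brackets to the comparative. Compared with smokers, their infants are expected to weigh more.
- **Primary outcomes, Table 2:** "Preterm birth • Low birth weight" share the obstetrics/neonatal column. No entry in the table is a continuous newborn measurement of size.
- **Secondary neonatal outcomes:** "Neonatal anthropometric measurements (weight in grams" and other body dimensions are listed here. Only the PEAPOD assessment in that list is limited to a subgroup.
- **Table 3:** LBW has a 5% baseline and a detectable OR of 1.74 at 400 per group, "detectable at a power of 80" per cent and "with a type I error rate of 0.05", using an uncorrected chi-square test.
- **Text after Table 3:** "LBW occurs at a frequency of about 5" per cent, and "Smoking has also been shown to increase incidence of LBW with an odds ratio of 1.75 (95% CI 1.42–2.10").
- **Table 4:** at 400 per group the detectable standardised mean difference is 0.20, given there for neurocognitive outcomes.

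**The concern.** The neonatal objective and the hypotheses ask whether babies differ in size. The primary outcome asks only whether they fall on one side of a threshold that about 20 of 400 controls (5%) would cross. A rare dichotomy usually carries much less information than the measurement behind it, and here that measurement is already planned.

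Table 3 hides the consequence. Its LBW entry of 1.74 sits just under the cited smoking OR of 1.75, so the outcome looks adequately powered. If that entry is wrong, a null LBW result would say little, and the article would have no correctly powered primary measure of newborn size.

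**Working it through.** **Inputs.** Control LBW rate 5%, smoking OR 1.75 (CI 1.42 to 2.10), 400 per group, alpha 0.05, uncorrected chi-square or t test: all from the article. The article does not state sidedness. Two-sided is used because it reproduces the other columns.

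**Step 1: the plan's own tables.** Solving for the OR that gives 80% power, for 100, 200, 300 and 400 per group:

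| Column | Stated | Recomputed |
|---|---|---|
| Wheeze, 10% | 3.00, 2.25, 1.96, 1.80 | 2.99, 2.25, 1.96, 1.81 |
| Preterm birth, 6.2% | 3.62, 2.63, 2.24, 2.04 | 3.63, 2.62, 2.24, 2.04 |
| LBW, 5% | 3.19, 2.26, 1.91, 1.74 | 4.01, 2.84, 2.41, 2.17 |
| Table 4 SMD | 0.40, 0.28, 0.23, 0.20 | 0.40, 0.28, 0.23, 0.20 |

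Only the LBW column fails. The fault is visible without calculation: at fixed n the detectable OR rises as the baseline falls from 10% to 6.2% (1.80 to 2.04), so it cannot then drop to 1.74 at 5%. One-sided testing gives 2.01 at 400 per group. Continuity-corrected, unpooled, log-OR, arcsine and unequal-allocation versions do not give 1.74 either; the nearest is 1.96, with 2:1 allocation.

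**Step 2: power of LBW at OR 1.75.**
- Exposed rate p2 = 1.75 × 0.05 / (0.95 + 1.75 × 0.05) = 0.0875 / 1.0375 = 0.0843. Difference 0.0343.
- Pooled rate 0.0672; null SE = √(2 × 0.0672 × 0.9328 / 400) = 0.0177.
- Alternative SE = √((0.05 × 0.95 + 0.0843 × 0.9157) / 400) = 0.0177.
- Power = Φ((0.0343 − 1.96 × 0.0177) / 0.0177) ≈ Φ(−0.02) = 49.2%.

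At OR 1.74 it is 48.3%. For 80% power at OR 1.75, 834 per group would be needed.

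**Step 3: the same LBW odds ratio as a shift in mean weight.** Assume normal weights, a common SD and a shift of the whole distribution.
- d = z(0.0843) − z(0.05) = −1.3765 + 1.6449 = 0.268 SD.
- SE = √(2/400) = 0.0707; power = Φ(0.268 / 0.0707 − 1.96) = Φ(1.84) = 96.7% (t test 96.6%). For 80% power, 218 per group.

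| LBW effect | Binary | Mean weight, pure shift |
|---|---|---|
| OR 1.42 (lower CI bound) | 21% | 65% |
| OR 1.75 | 49% | 97% |
| OR 2.10 (upper CI bound) | 76% | 99.9% |
| Half the log-odds effect (OR 1.32) against controls | 15% | 46% |
| The remaining half, against smokers | 18% | 49% |

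The last two rows illustrate vapers lying midway between controls and smokers. The article gives no vaping effect.

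**Step 4: dependence on the shift assumption.** Hold the LBW OR at 1.75; the binary benchmark stays at 49%.
- Exposed SD 5% larger: mean difference = 1.6449 − 1.05 × 1.3765 = 0.200; SE = √((1 + 1.05²)/400) = 0.0725; power 79%.
- Exposed SD 10% larger: mean difference 0.131, SE 0.0743, power 42%.
- If 75%, 50%, 25% or 0% of the excess LBW comes from a general shift and the rest from the lower tail only, power is 89%, 73%, 45% or 18%.

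**The case against.** The strongest reply is that LBW is a legitimate primary outcome. The primary obstetric objective concerns the risk of adverse outcomes, Table 2 groups obstetric and neonatal outcomes together, and the hypothesis against non-smokers carries the LBW tag. Birth weight in grams and birth centile are already planned as secondary outcomes, so the neonatal objective is not ignored. This stands as far as it goes: LBW need not be dropped. It does not explain why the separate neonatal objective has no matching continuous newborn measure in Table 2.

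The second reply is that an odds ratio for LBW does not determine a mean difference. The two are different estimands, and the article gives neither a birth-weight SD nor a target difference. This stands in full.

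Several stronger readings are tempting and are not supported:
- A reader might infer that changing the outcome takes power from 49% to 97% at no cost. The 97% needs a pure shift with equal SD, and the change of estimand is itself a cost.
- A reader might infer that mean weight can lose only if the effect lies wholly in the tail. Step 4 shows that it already loses with a 10% larger exposed SD, or with a quarter of the excess coming from a general shift.
- A reader might add that LBW duplicates preterm birth. The article does not quantify that overlap, and mean weight also depends on gestational age, so the change would not separate the two.
- A reader might take 97% as the power for vaping. OR 1.75 compares smokers with non-smokers.

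That every infant has a weight in grams is also an inference, although LBW cannot be classified without one.

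**Conclusion.** The concern holds in conditional form. The primary neonatal question is worded as a difference in weight but is tested through a 5% dichotomy. At 400 per group that dichotomy has about 49% power at the cited OR of 1.75, not the roughly 80% that Table 3 implies; the detectable OR is 2.17. This part rests only on the article's inputs and two-sided testing.

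The advantage of mean weight rests on an assumption that the article neither makes nor excludes. Where most of the effect is a general shift with similar SDs, the advantage is large (up to 97% against 49%). It shrinks as the exposed SD grows or the effect concentrates in the lower tail, and it can reverse. For a vaping contrast of half the log-odds size, even the favourable case gives only about 46%, so the change would improve power without making it adequate. These figures allow for no attrition.

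**What to change.** Make birth weight in grams the primary, or a co-primary, neonatal outcome. Compare vapers with each reference group by linear regression with robust standard errors, which also allow for unequal SDs, adjusting for the planned confounders. State the assumed SD and target difference, and cite Table 4's 0.20 SD at 400 per group as the detectable effect. For illustration, with an assumed SD of 450 to 550 g, 0.20 SD is 90 to 110 g.

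Keep LBW as a key secondary or co-primary outcome, and birth centile as planned. Correct the LBW column of Table 3 to 4.01, 2.84, 2.41 and 2.17 whichever outcome is primary.

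The cost is protocol wording and the choice of a defensible SD and target difference; no new measurement is needed. The real downside is that the headline becomes a mean difference instead of a clinical threshold, which is why LBW should remain prominent.
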